### Outcome variables and assessments

Table 3 describes the study measures. The primary outcomes were change in weight and BMI. Secondary outcomes were waist circumference, blood pressure, physical activity and diet. Surveys additionally collected information on participant psychosocial and socio-demographic characteristics. Because of threat to contamination, we included a series of questions asking about participants’ potential knowledge of and discussions with other members of the study in the follow-up surveys. Surveys were verbally administered by trained research staff to ensure a higher completion rate given varying literacy levels of participants. In addition, the study examined potential external validity and sustainability of the Fresh Start intervention on measures of reach, adoption, implementation and maintenance, consistent with the RE-AIM framework [36].

**Table 3 Tab3:** Measurement protocol in the Fresh Start study

Measure	Assessment approach/tool
Weight/BMI	Measured with the individual wearing light clothing and no shoes using portable digital scales and stadiometers
Waist circumference	Measured twice (and averaged) with a non-stretchable measuring tape using standard methodology
Blood pressure	Measured three times over 60–90 min in a standardized manner [42], after several minutes of quiet sitting with a Dinamap XL automated BP monitor [43]
Physical activity	The Pregnancy Physical Activity Questionnaire [44]
Diet and Eating Behaviors	NCI computerized 24 h recall [45], Three-Factor Eating Questionnaire, Weight Behavior Inventory [46]
Other behaviors	Pittsburgh Sleep Quality Index [47], daily weighing, Behavioral Risk Factor Surveillance System tobacco use questions, CAGE alcohol screening questionnaire
Psychosocial	Edinburgh Postnatal Depression Scale [48], Perceived Stress Scale [49], Delaying Gratification Index (food questions), perceived weight status (investigator developed), family social support for weight loss (investigator-developed)
Socio-demographics	Education, income, employment, race/ethnicity, age, marital status, living situation, number of children, smoking, weight history, parity, breastfeeding and chronic conditions.
Reach	Number, percentage and representativeness of women who participate in the study, including recruitment and retention rates and attendance at intervention sessions.
Adoption	Counts of uptake of the intervention by new WIC clinics after the research study, assuming effectiveness

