### Planned analyses

Analysis to test the study hypotheses will be conducted in Spring, 2017 when the 12-month follow-up data collection is completed. The longitudinal aspect of the design involves repeated measures at three time points (baseline, and 6 and 12 months post-intensive intervention). To accommodate the correlation between baseline and subsequent time points we plan mixed models regression for primary and secondary analyses. The main predictors of the model include intervention indicator, time points, and the interaction term between intervention indicator and time points. The treatment effects will be evaluated by testing the interaction term of time and the indicator of intervention. We will use exploratory graphical analysis to examine the relationship of the outcome of interest and baseline factors not in balance to determine the functional form of the model fit. Upon determining the best models, we will then include an indicator of the intervention group to estimate and test the effect of the intervention. Model building strategies described by Harrell [37] will be used to build the multivariable models. There is always the chance that some unmeasured confounder could impact on the results. We will estimate the strength of the confounding that would be necessary to eliminate any measured differences between intervention and comparison groups through sensitivity analyses [38, 39]. We will explore site-level effects by estimating random effects models, although we do not anticipate such an effect.

All primary analyses will be conducted on an “intent-to-treat” basis with each patient enrolled in the intervention group analyzed as part of the group, regardless of engagement with the intervention. Additionally, multiple imputation methods will be used to account for those lost at the follow-up sessions.

Planned analyses also include assessing the potential external validity and sustainability of the Fresh Start intervention on measures of reach, adoption, implementation and maintenance, as described in Table 3. Descriptive statistics (i.e. counts, proportions, means) will be used to describe each of these measures.

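### The planned arm-by-time model lets each randomised arm have its own baseline mean; the test is valid, but a baseline-adjusted version would be more precise at no cost, mainly for secondary outcomes

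*Protocol article*

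**What the plan says.** The Planned analyses section of the protocol article describes "repeated measures at three time points (baseline, and 6 and 12 months post-intensive intervention", so baseline belongs to the outcome vector. It lists the terms: "The main predictors of the model include intervention indicator, time points, and the interaction term between intervention indicator and time points". The effect is judged on the interaction: "The treatment effects will be evaluated by testing the interaction term of time and the indicator of intervention". The scope is general: "we plan mixed models regression for primary and secondary analyses".

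Under Outcome variables and assessments, "The primary outcomes were change in weight and BMI", and "Secondary outcomes were waist circumference, blood pressure, physical activity and diet". For loss to follow-up, "multiple imputation methods will be used to account for those lost at the follow-up sessions".

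The article does not say that the arms share a baseline mean, or that the baseline value of each outcome is a covariate. The only covariate wording concerns baseline factors found to be out of balance, followed by general multivariable model building.

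**The concern.** Participants are randomised, so the expected baseline difference between arms is zero. A model with an arm main effect estimates that difference from the data all the same and subtracts it in full from the follow-up difference. The result is a change-score comparison. When baseline and follow-up are only moderately correlated, subtracting the whole baseline value adds noise.

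What is at stake is the width of the confidence intervals, and hence the power, for waist, blood pressure, physical activity and diet. The power calculation covers weight only, so nothing else in the article protects precision on these outcomes. The baseline values needed to recover the loss are already collected.

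**Working it through.** **Inputs from the article.** Pilot SD of weight change 8.2 lb, assumed difference 5.0 lb, two-sided alpha 0.05, power 85%, 50 per group (Statistical approach and power). Baseline SDs: BMI 6.46 kg/m², waist 3.91 inches (Table 1).

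**Inputs assumed.** Mean height about 1.62 m, the correlation r for each secondary outcome, the SD of waist change, and equal SDs over time unless stated otherwise.

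**1. The plan's own figure.** n per arm = 2 × (1.960 + 1.036)² × 8.2² / 5.0² = 48.3, so 49 by the normal approximation. The exact t calculation gives 84.8% power at 49 and 85.5% at 50. The stated 50 per group is reproduced. It is built on the SD of change, so it already matches the planned contrast.

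**2. What the interaction estimates.** With arm, time and arm-by-time terms the mean model is saturated. With complete data, the interaction at a follow-up visit is (intervention follow-up mean − intervention baseline mean) − (control follow-up mean − control baseline mean). In simulated complete data with 50 per arm, the fitted interaction equalled the raw difference in mean change at both visits. Adding a time-constant baseline covariate as a main effect left it unchanged.

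**3. Relative variance.** Let σ be the SD at each visit.
- Planned contrast, per participant: 2σ²(1 − r)
- Baseline-adjusted contrast: σ²(1 − r²)
- Ratio: (1 − r²) / [2(1 − r)] = (1 + r)/2

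With unequal SDs σ_B (baseline) and σ_F (follow-up), the planned variance is σ_F²(1 − r²) + (σ_B − rσ_F)². In large samples adjustment is therefore never less precise.

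**4. Weight.** SD of weight ≈ 6.46 × 1.62² × 2.205 = 37.4 lb. Then r = 1 − 8.2² / (2 × 37.4²) = 0.976, and the ratio is (1 + 0.976)/2 = 0.988. Heights of 1.55 to 1.65 m give r of 0.971 to 0.978 and ratios of 0.986 to 0.989. The gain is about 1%. The same holds for BMI, because an adult's height does not change.

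**5. Secondary outcomes, over assumed r.**

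| r | Variance ratio | Variance reduction |
|---|---|---|
| 0.4 | 0.70 | 30% |
| 0.5 | 0.75 | 25% |
| 0.6 | 0.80 | 20% |
| 0.7 | 0.85 | 15% |
| 0.8 | 0.90 | 10% |
| 0.9 | 0.95 | 5% |

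On the standard-error scale, √0.70 = 0.837 and √0.95 = 0.975, so intervals would be about 16% to 2.5% narrower. A generalised least squares fit with a common baseline mean gave 0.70, 0.80 and 0.90 at r = 0.4, 0.6 and 0.8. With about 17% missing at 12 months and no imputation, the ratios were 0.74, 0.82 and 0.91.

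**6. Waist.** r = 1 − (SD of change)² / (2 × 3.91²). An assumed change SD of 1.5 inches gives r = 0.926 and a ratio of 0.96. At 3.5 inches, r = 0.60 and the ratio is 0.80. The gain lies between about 4% and 20%.

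**The case against.** The strongest reply is that the planned analysis is conventional and correct. Under randomisation it is unbiased with the right type I error, it matches primary outcomes defined as change, and it agrees with a sample size based on the SD of change. All of that stands. The point is about efficiency only.

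Four stronger readings are tempting, and the article does not support them.

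- **The primary result is compromised.** A reader might infer this because the same model serves all outcomes. By the article's own SDs, weight loses about 1% of precision, and 50 per group stands.
- **Chance baseline imbalance biases the effect.** A reader might count regression to the mean as a second harm. Over randomisations there is no bias, and the planned standard error already contains this variation. The identity 2(1 − r) = (1 − r²) + (1 − r)² shows it: the last term is the variance due to chance imbalance, and it is exactly the loss computed above.
- **A specific large loss.** At r = 0.5, adjustment would be worth 1/0.75 = 1.33 times the participants, and would lift a contrast with 80% power to about 90%. But both that r and the 80% starting point are hypothetical; the article states neither for any secondary outcome.
- **All four secondary outcomes lose equally.** Table 3 has waist measured twice and averaged and blood pressure measured three times. Replicates tend to raise r. A sizeable loss is more plausible for diet by 24 h recall and activity by questionnaire.

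It can also be said that this is a condensed article with room for further model building. However, the article states the terms and the test, and the point concerns that stated model. Adjusting for factors out of balance does not cure it: the adjustment is conditional, does not name the baseline value of the outcome, and as a main effect leaves the interaction unchanged.

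**Conclusion.** The point holds as a minor, avoidable loss of precision, mainly on secondary outcomes. The planned interaction test is valid, and the sample size is unaffected. For weight and BMI the gain is negligible, about 1%, assuming a height near 1.62 m and that the pilot SD of change applies at the follow-up visits. For the secondary outcomes the size is not known from the article. Over an assumed r of 0.4 to 0.9 the variance would fall by 30% to 5%, somewhat less with dropout if incomplete data are fitted directly. The gain is likely to be largest for diet and physical activity, and smaller for waist and blood pressure. The (1 + r)/2 figures assume equal SDs over time. The equivalence to a change score is exact for complete data, and so within each imputed data set.

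**What to change.** Keep the mixed model and change its baseline specification, in one of two ways:

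- Keep baseline in the outcome vector, but constrain the arms to a common baseline mean: drop the arm main effect and keep time and arm-by-follow-up-time terms.
- Model the 6- and 12-month values, with the baseline value of that outcome as a covariate.

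Report the arm difference at each visit from that model. Use the same form for primary and secondary outcomes for consistency, although weight and BMI will hardly change.

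The cost is one sentence of analysis wording, best settled before outcomes are examined by arm. It needs no new data and no change in sample size, and it keeps validity under randomisation.

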### Study site and participants

Study participants were 139 clients served by 5 WIC clinics in Worcester, MA. Eligibility criteria included: 1) childbirth in the previous 6 weeks to 6 months; 2) age 18 and over; 3) body mass index (BMI) ≥ 27 kg/m^2^; 4) English-speaking; and 5) obstetric provider approval for participation in the diet and physical activity components of the intervention and weight loss. Exclusions included: 1) being unable or unwilling to give informed consent; 2) being pregnant or planning to become pregnant within the following 24 months; 3) having a psychiatric illness which limits ability to participate; 4) taking a medication that causes weight changes; 5) having no telephone; and 6) planning to move out of the area within the study period.

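### Chance baseline imbalance, and how the unbalanced factors relate to the outcome, are allowed to shape the model for the intervention effect, and no single primary model is named

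*Protocol article*

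**What the plan says.** All of this is in the protocol article, under Planned analyses.

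- Scope: "we plan mixed models regression for primary and secondary analyses".
- Fixed terms: "The main predictors of the model include intervention indicator, time points, and the interaction term between intervention indicator and time points". Baseline weight is one of the three repeated outcome measures, and the treatment effect is to be judged by the interaction.
- Covariates: the plan calls for "exploratory graphical analysis to examine the relationship of the outcome of interest and baseline factors not in balance", and the stated purpose is "to determine the functional form of the model fit".
- Order: "Upon determining the best models, we will then include an indicator of the intervention group to estimate and test the effect of the intervention".
- Method: "Model building strategies described by Harrell [37] will be used to build the multivariable models".

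The article gives no criterion for imbalance and no candidate list. It does not mark the model-building step as secondary or exploratory. The treatment effect is thus described twice, once as the interaction in a fixed model and once as an indicator added to a model built from the data. Neither is named as the primary analysis.

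**The concern.** Randomisation makes baseline differences a matter of chance, so observed imbalance says nothing about whether a factor is worth adjusting for. What makes adjustment worthwhile is a relation to the outcome that can be expected in advance. If only unbalanced factors are examined, a strong predictor that happens to be balanced is passed over, and a weak one that happens to be unbalanced may enter.

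Two things are at stake. The first is precision: the rule may recover little of what a fixed prognostic list could give. The second is the status of the primary estimate, because the covariate set changes with the data and with judgement about plots, so two careful analysts could reach different primary models.

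The article already points to candidates that need no new data. Delivery date is checked at screening, and eligibility spans "childbirth in the previous 6 weeks to 6 months". Breastfeeding and parity are in Table 3, and the intervention sets different calorie goals by breastfeeding status.

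**Working it through.** **Inputs from Statistical approach and power.** Difference 5.0 lb (−5.0 against 0), SD of change 8.2 lb, two-sided alpha 0.05, power 85%, 50 per group, target 120, enrolled 139. **Assumed, because the article does not give them:** R² of the covariates for weight change, the number of candidates and the selection cut-offs.

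**1. The plan's own figure.** With SE = 8.2 × √(2/50) = 1.64 lb, the noncentrality is 5.0/1.64 = 3.05. The noncentral t distribution on 98 degrees of freedom gives 85.5% power, so 50 per group reproduces. That calculation is unadjusted and does not depend on any covariate.

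**2. What fixed covariates could add.** Residual SD = 8.2 × √(1 − R²), then as in step 1. The few degrees of freedom spent on covariates are ignored.

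| Assumed R² | Residual SD (lb) | Power, 50 per arm | Power, 60 per arm |
|---|---|---|---|
| 0 | 8.20 | 85.5% | 91.2% |
| 0.05 | 7.99 | 87.2% | 92.5% |
| 0.10 | 7.78 | 88.9% | 93.7% |
| 0.20 | 7.33 | 92.1% | 95.9% |

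**3. What choosing by imbalance recovers.** Change scores were simulated with 50 per arm and 10 candidate factors, 3 of them prognostic. Unbalanced meant p < 0.10. A second version of the rule also required p < 0.10 for the relation to the outcome. There were 6,000 trials per setting, so the Monte Carlo standard error is about 0.5 points for power and 0.3 for null rejection.

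| R² | Unadjusted | By imbalance | Imbalance and outcome | Fixed prognostic |
|---|---|---|---|---|
| 0.10 | 85.2% | 84.4% | 84.4% | 87.5% |
| 0.20 | 85.5% | 85.2% | 85.1% | 91.3% |
| 0.30 | 86.2% | 86.2% | 86.7% | 94.4% |

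A second set-up had 8 candidates, 2 of them prognostic with r = 0.3 each, and selection at imbalance p < 0.2 and outcome p < 0.1. It gave 85.4% unadjusted, 86.1% under the rule and 90.9% with fixed covariates. The rule kept both real predictors in about 3% of trials and neither in about 68%.

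**4. How often the covariate set depends on chance.** With 10 independent candidates, the probability of at least one imbalance at p < 0.10 is 1 − 0.9¹⁰ = 65%. The simulation agrees (65–66%).

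**5. Type I error.** Applied mechanically, the rule rejected a true null in 3.5–4.6% of trials across both set-ups, so it is slightly conservative. Taking the smallest p-value among the unadjusted and two selected models gave 5.4–6.6%. That is about one point above the unadjusted test in the same runs (4.5–5.5%).

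**6. Does this carry over to the planned mixed model?** Let Δȳ_k be the difference between arms in mean weight at visit k, and Δz̄ the difference in a baseline covariate. With complete data and the covariate as a main effect (coefficient γ), the interaction estimate is

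(Δȳ_k − γΔz̄) − (Δȳ_0 − γΔz̄) = Δȳ_k − Δȳ_0.

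The covariate cancels. Generalised least squares under two covariance structures confirmed that the estimate and its standard error do not change. With 25% missing at each follow-up, the estimate moved by at most 0.08 lb. If the covariate also enters by time, the estimate becomes (Δȳ_k − Δȳ_0) − (γ_k − γ_0)Δz̄, and adjustment then matters. Steps 2 to 5 therefore describe a change-score model, or a mixed model with covariate-by-time terms.

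**The case against.** The case against is substantial.

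- **Stated purpose.** The quoted step is aimed at functional form, and the article never says that balanced prognostic factors are left out. That is literally so. Still, the look is confined to unbalanced factors, and the next sentences build multivariable models and choose the best among them, so selection is the natural reading. A candidate list may exist in a plan that is not shown, but it would have to replace the rule stated here.
- **Steering.** The indicator enters after the model is settled, which limits steering by the treatment result. This stands. A reader might infer that the test has an inflated size, but step 5 does not support that. The figure near 6% needs a choice of the smallest p-value, which the article does not plan.
- **Model.** A baseline covariate entered only as a main effect leaves the planned interaction essentially unchanged. This stands. The article does not say how covariates would enter, so the harm depends on an unstated choice.
- **Power.** Sample size does not rely on adjustment, and the rule loses almost nothing against an unadjusted test. With all 139 women analysed, unadjusted power is about 95%. This also stands: what is given up is an available gain, and the trial is not made underpowered.
- **Time since delivery.** One might argue that the eligibility window is when weight changes most. The Background does not support this, since it describes loss in the first 6 weeks and then a plateau or gain in many women. Weeks since delivery is a plausible covariate, not a proven strong one.

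**Conclusion.** The point holds as a badly fixed analysis rule that should be corrected. Covariates shaped by chance imbalance bring almost no precision, and the article leaves open whether the fixed interaction model or the data-built model gives the primary result.

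For assumed R² of 0.05–0.20 the forgone gain is about 2 to 7 power points at 50 per arm and 1 to 5 at 60 per arm. Near R² = 0.05 it is under 2 points. These sizes rest on an R² the documents do not give and on a change-score analysis or covariate-by-time terms; the simulated performance of the rule also rests on assumed cut-offs. The data-dependence of the primary model rests on the wording alone and needs none of these assumptions.

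It would go too far to infer that the test is materially anti-conservative, that the sample size is wrong, or that every choice of covariates would move the planned interaction estimate.

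**What to change.** Before the Spring 2017 analysis, replace the imbalance-driven step under Planned analyses with:

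1. **One named primary model**, stating which term or contrast is the primary test.
2. **A short fixed list of covariates already collected**, chosen for expected prognosis, each with its functional form. Examples are weeks since delivery at baseline, breastfeeding at baseline, parity and site. If site is included, align this with the exploratory random-effects step for site.
3. **A stated way of entering them.** Either use covariate-by-time terms in the planned mixed model, or use covariates in a follow-up or change model adjusted for baseline weight. Do not enter baseline weight as a covariate while it is also in the outcome vector.
4. **The unadjusted intervention-by-time model reported beside it**, with any imbalance-driven or data-built model labelled exploratory.

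The cost is a few sentences and a few degrees of freedom, with no new data. If the covariates prove weakly prognostic there is little gain in precision, but the primary estimate is still fixed in advance.

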
### Intervention format and objectives

The Fresh Start intervention protocol included eight in-person 90-min weekly group sessions (intensive phase) followed by 9 monthly individual telephone follow-up calls. A WIC program nutritionist implemented the group intervention sessions and calls following a detailed provider manual. The nutritionist was trained in behavioral weight loss strategies, principles of motivational interviewing and the use of the Fresh Start intervention tools. A WIC assistant made reminder calls prior to each session, conducted weigh-ins at the beginning of each session and assisted participants with recording and graphing their weight in a program sheet. The weight loss and associated behavioral objectives included weight loss of 1–2 lb per week by working toward a goal of consuming approximately 1500 and 2000 calories for non-breastfeeding and breastfeeding mothers, respectively, and walking 10,000 steps (or equivalent) per day.

The group sessions were interactive and built on one another. Participants were instructed to track their physical activity, diet and weight in between sessions. Sessions began with a review of the participants’ records since the previous session and discussion of successes and challenges to goal achievement, followed by a review of the previous session. A storytelling video relevant to the session topic (topics depicted in Table 2) was then shown, followed by a guided discussion that intended to highlight the women’s experiences regarding the topic being presented. Group discussions were intended to promote modeling opportunities among the women by highlighting similarities among women and exploration of challenges to behavior change and successful strategies to overcome them. Sessions also sought to promote support among participants (i.e., encouragement to exercise together). All sessions concluded with goal-setting.

**Table 2 Tab2:** Fresh Start intervention session topics

Session #	Topic(s)
1.	Exploring and sharing weight loss motivations; Getting started at being active; Introducing goal setting
2.	Tracking food and beverage intake to make better eating choices
3.	Identifying problem eating habits; Three ways to reduce calories
4.	Reading nutrition labels; Making dietary modifications
5.	Cutting calories on a budget
6.	Taking charge of the environment: Food cues
7.	Taking charge of what’s within you: Talking back to negative thoughts
8.	Dealing with slips; Staying motivated

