### Statistical approach and power

Sample size calculations were based on the primary hypothesis that participants in the Fresh Start intervention would demonstrate greater weight loss than participants in the comparison condition at 6 and 12 months follow-up. In our pilot, we observed a weight change of -4.6 lbs (SD = 8.2lbs). Assuming the Fresh Start intervention would yield a similar change of -5.0 lbs and conservatively that the comparison condition would maintain their weight (0 lbs change), a two-sided, two-sample *t*-test of means with alpha = 0.05 and 85 % power indicates that enrolling 50 people per group would allow us to detect the desired difference. Thus, the original target sample size was 120 participants based on power calculations. We exceeded this goal, enrolling 139 participants.

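### The session group, present in the intervention arm only, is missing from the stated primary model and from the sample size; if outcomes correlate within groups, type I error exceeds 5%

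*Protocol article*

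**What the plan says.** **Delivery (Intervention format and objectives; Comparison condition).** The intervention consists of "eight in-person 90-min weekly group sessions (intensive phase) followed by 9 monthly individual telephone follow-up calls". Interaction between members is part of how it is meant to work: "Group discussions were intended to promote modeling opportunities among the women by highlighting similarities among women". The sessions also aim to build mutual support. Comparison women get the print materials by post and a fitness membership, with no group contact.

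**Analysis (Planned analyses).** Mixed models are chosen to handle correlation between a woman's baseline and later measurements. The main predictors are arm, time and arm × time, and the treatment effect is tested through the interaction. One further sentence concerns clustering: "We will explore site-level effects by estimating random effects models, although we do not anticipate such an effect".

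**Sample size (Statistical approach and power).** A two-sided, two-sample t-test with a 5.0 lb difference and a pilot SD of 8.2 lb leads to the statement that "enrolling 50 people per group would allow us to detect the desired difference", at 85% power. The enrolment target was 120, and 139 women were enrolled. No group size, ICC or design effect appears.

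**The concern.** This is a partially nested design: women in one arm share a session group, and women in the other do not. A programme that relies on members influencing one another gives good reason to expect some correlation between their outcomes. Such correlation adds a between-group component to the variance of the intervention-arm mean. A model whose only stated dependence is within a woman over time leaves that component out of the standard error.

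Clinic does not stand in for session group. The article does not equate the five WIC sites with the session groups, and the site models are exploratory and separate from the primary test.

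The stake is the primary conclusion. The error runs towards declaring the intervention effective, in a trial meant to inform wide uptake in WIC clinics. The power statement rests on the same independence assumption.

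**Working it through.** **Inputs from the article:** difference 5.0 lb; SD of weight change 8.2 lb; two-sided alpha 0.05; 50 per group for 85% power; target 60 per arm; 139 enrolled.

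**Assumptions, because the article gives no figure:** women per session group m; ICC of weight change within a group; a near-even split of the 139 (69 and 70). The calculations compare mean change between arms at one follow-up, as the article's own power calculation does.

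**1. The plan's own figure.** Normal approximation: n = 2 × [8.2 × (1.960 + 1.036) / 5]² = 48.3, so 49 per arm. By the noncentral t, 50 per arm gives 85.5% power. The stated figure reproduces, under independence.

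**2. Effect of clustering in one arm.** The design effect in the intervention arm is DE = 1 + (m − 1) × ICC. With equal arms, the true SE exceeds the SE that ignores groups by the factor k = √[(DE + 1)/2]. The actual two-sided type I error is then about 2 × [1 − Φ(1.96/k)].

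Example, m = 10 and ICC 0.05: DE = 1.45; k = √1.225 = 1.107; 1.96/1.107 = 1.771; type I error = 7.7%.

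| ICC | m = 7: k | formula | simulated | m = 10: k | formula | simulated |
|---|---|---|---|---|---|---|
| 0.01 | 1.015 | 5.4% | not run | 1.022 | 5.5% | not run |
| 0.02 | 1.030 | 5.7% | 5.7% | 1.044 | 6.1% | 6.4% |
| 0.05 | 1.072 | 6.8% | 6.8% | 1.107 | 7.7% | 7.9% |
| 0.10 | 1.140 | 8.6% | 8.6% | 1.204 | 10.4% | 10.8% |

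The simulated columns are 20,000 runs of a t-test that ignores groups, with 70 women per arm (10 groups of 7, or 7 groups of 10). A second set of 20,000 runs agreed within simulation error.

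**3. Power.** SE = 8.2 × √(DE/n₁ + 1/n₀), and power ≈ Φ(5/SE − 1.96).

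- 50 per arm, m = 8, ICC 0.05: DE = 1.35; SE = 8.2 × √(2.35/50) = 1.778; 5/1.778 = 2.813; power 80.3%.
- 60 per arm, same m and ICC: SE = 8.2 × √(2.35/60) = 1.623; 5/1.623 = 3.081; power 86.9%.

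In the table, the first figure is this normal approximation. The second uses a noncentral t with degrees of freedom based on the number of groups.

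| m, ICC | 50 per arm | 60 per arm | 69 and 70 |
|---|---|---|---|
| 8, 0.01 | 85.0 / 80.9% | 90.7 / 88.1% | 94.2 / 92.5% |
| 8, 0.05 | 80.3 / 74.8% | 86.9 / 83.1% | 91.2 / 88.6% |
| 8, 0.10 | 74.7 / 67.8% | 82.0 / 76.9% | 87.1 / 83.3% |
| 10, 0.05 | 78.7 / 70.8% | 85.5 / 80.0% | 90.1 / 86.1% |
| 10, 0.10 | 71.6 / 61.8% | 79.2 / 71.7% | 84.7 / 78.8% |

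The last column assumes that every enrolled woman is analysed. Loss to follow-up uses up the same margin: the 139 fall to 100, or 50 per arm, at 1 − 100/139 = 28% loss.

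**The case against.** **Everything about size is assumed.** This stands. The article gives neither group size nor ICC, and at ICC 0.01 the distortion is trivial. Some features favour a small ICC: the group phase lasts eight weeks, outcomes are measured 6 and 12 months after it, individual calls follow, a detailed manual is used, and attendance was limited in the pilot. None of this shows the ICC to be zero, but the 0.10 row should not be read as the expected case.

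**The trial is larger than 50 per arm.** This also stands. A reader might infer that the trial as enrolled fails to deliver 85% power. The documents do not support that: at 60 per arm, groups of 8 and ICC 0.05 give 86.9% (83.1% with group-based degrees of freedom), and more if most of the 139 are analysed. Extra enrolment does not, however, correct a standard error that omits a variance component.

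**The plan does allow for some dependence.** A reader might also infer that all women are treated as independent. That is too broad. Within-woman correlation is modelled, site is to be explored, and treating comparison women as independent is right. The gap is confined to intervention women who share a session group.

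**The SAP is not shown and could add a group term.** Possible. But the article itself states why it uses a mixed model, its main terms, the test, a clustering provision at clinic level and the power method. The point concerns what is stated, and the power basis would need restating in any case.

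**Conclusion.** The point holds in a limited form. The stated primary model and sample size leave out session-group clustering in the intervention arm, and the site exploration does not replace it. For any positive within-group ICC, the standard error of the arm × time effect is too small and type I error is above 5%. With groups of 7 to 10 and 70 women per arm, the excess is slight at ICC 0.01; type I error is about 6% at 0.02, 7 to 8% at 0.05 and 9 to 11% at 0.10.

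On power, 85% at 50 per group holds only under independence. Whether the trial as enrolled reaches 85% depends on ICC, group size and loss to follow-up, none of which the article gives, so no shortfall can be asserted.

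**What to change.** 1. In the primary model, add a random effect for session group in the intervention arm only, treating each comparison woman as her own cluster.
2. Define the group as the one to which the woman was assigned, including women who never attended, to stay consistent with intention to treat. The article mentions attendance counts but not group identity, so confirm that assignment was recorded.
3. Use small-sample degrees of freedom, such as Kenward-Roger or Satterthwaite.
4. Report the estimated ICC.
5. Restate power over a range of ICCs and group sizes at the numbers analysed.

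Fixed effects for site are optional and not part of this correction.

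The cost is a few lines of analysis text, slightly wider intervals and a somewhat lower quoted power. Part of that cost remains even if the ICC is zero: with groups of 8 and group-based degrees of freedom, power is 82.4% rather than 85.5% at 50 per arm, and 89.3% rather than 91.2% at 60. The article places the analysis in the future, so the change can be fixed before the hypotheses are tested.
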